##### Evaluation

Reported patient reach data and site-specific online accesses of the conversation aids will be counted for each site monthly. We will calculate patient reach as the percentage of eligible patients receiving the Option Grid or Picture Option Grid. We will report this overall and by site for sites with sufficient data. In the patient reach email response from sites, any details given regarding barriers and facilitators to patient reach will be noted and responded to, as appropriate.

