#### Reach

##### Data collection

Our primary outcome is patient reach, which is defined as the number of patients who are given the opportunity to use one of the conversation aids over the number of eligible patients, by site. Surgeons using the conversation aids at each site will determine patient eligibility based on clinical judgment. We will determine patient reach for each site on a monthly basis using the following data:Reported uses of the conversation aids—We will email each site monthly to request data and notes for the previous month regarding patient reach. Other uses of the conversation aids can include using paper copies, sending links or PDFs to patients by email, patient portal, EHR, or other distribution methods.From our experience, we anticipate that paper versions will be used only once with patients [11]. However, we realize a patient may be given multiple copies throughout their care and/or for others to view (family members, friends, caregivers). While this may occur, we do not anticipate our sites to regularly provide multiple paper copies of an Option Grid/Picture Option Grid. In the instance multiple copies are given, we will work with each site to try and get as accurate of count as possible.Online access to conversation aids via platform—The SHAIR Collaborative website is able to track the downloads of the conversation aids or clicks out to the linked EBSCO website for the interactive tools. Downloads will be tracked and reported on a monthly basis.

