#### Adoption

##### Data collection

Our main measure of adoption is the total number of SHAIR Collaborative sites that actively participate. Sites that are interested in joining the SHAIR Collaborative will sign a letter of support. We will note when sites join the SHAIR Collaborative and if they become inactive (based on lack of responsiveness or signaling their resignation). We will recruit additional sites routinely throughout the project guided by stakeholder feedback.

Additionally, we will conduct brief interviews with SHAIR site champions (clinical and non-clinical) approximately 1 year into implementation and again towards the end of the formal implementation period before sustainability. The interview guide will be designed using Diffusion of Innovation and other relevant frameworks [25]. Interviews will be first conducted with phase 1 sites and then phase 2 sites, as relevant.

Lastly, we will measure social interconnectedness within SHAIR Collaborative over time utilizing quarterly online surveys to active SHAIR Collaborative members. The surveys will include identifying names and the number of contacts made within the Collaborative [38].

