### Data management

Patient reach data and implementation facilitating data will be tracked via spreadsheets and stored in a shared project folder. Survey data will be stored in the Dartmouth Qualtrics database, a HIPAA-compliant web-based data management system. Dartmouth project staff will not have access to the EHRs at any participating phase 1 or phase 2 sites. Our database management system is designed to comply with the ICH Good Clinical Practice guidelines. For statistical analysis, data will be downloaded and stored on an encrypted hard drive owned by Dartmouth College.

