One practical limitation in this project is the challenge of engaging with busy clinicians. It is important to be willing to tailor the communication strategy to our sites in order to improve engagement. There is also a balance between under- and over-communicating, making it important to focus on the necessary items (especially pertaining to sustainability) to cover with clinicians. Another practical limitation is the generalized nature of the Option Grid conversation aids. Feedback regarding the statistical content on Option Grids is often site-specific, so we consistently suggest to use the conversation aids flexibly, allowing for adaptations for individual patients. One major strength of this project is the support from ASBrS, ensuring better chances at sustaining the whole or parts of the SHAIR Collaborative when the project funding is over. The support from our community-based partnerships, especially patient partners, provides a strong and diverse stakeholder group ensuring all voices are heard, which may help with sustainability. Another strength is the SHAIR Collaborative platform itself—open-access, completely online, and ability to support sites from across North America. We are also using well-established frameworks throughout the creation, data collection, and evaluation of the project: Diffusion of Innovation, RE-AIM, Normalization Process Theory, and FRAME and FRAME-IS [25, 31, 40, 42].

We will participate in numerous dissemination activities through conferences and other communication platforms. We will also engage all project stakeholders in the dissemination of our project findings.

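### Overall reach rests only on site-months that were reported, and non-reporting is plausibly tied to low reach; bounds over all sites that began implementation should stand beside it

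*Protocol article*

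**What the plan says.** The protocol article, Reach, data collection, gives the outcome: "Our primary outcome is patient reach, which is defined as the number of patients who are given the opportunity to use one of the conversation" tools, divided by the number of eligible patients, by site. The main source is a request to the sites: "We will email each site monthly to request data and notes for the previous month regarding patient reach". Eligibility is settled locally: "Surgeons using the conversation aids at each site will determine patient eligibility based on clinical judgment". A second source is website tracking of downloads and of clicks through to the interactive tools: "Downloads will be tracked and reported on a monthly basis".

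The Reach evaluation section expresses reach as a percentage and adds: "We will report this overall and by site for sites with sufficient data".

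Four other places bear on this:

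- Adoption, data collection: the team notes when sites join and "if they become inactive (based on lack of responsiveness or signaling their resignation").
- Adoption, evaluation: the numbers of active and inactive sites, and the proportion of joining sites still active, are reported at the end of funding.
- Table 1 and Implementation, evaluation: a site scores yes for communications engagement in a month if it was in touch at least once, and returning its patient uses is the example given. That factor is then a candidate predictor of high reach.
- Data management: "Dartmouth project staff will not have access to the EHRs at any participating phase 1 or phase 2 sites".

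**The concern.** A percentage needs a denominator, and here the only denominator is what a site chooses to send. If the sites and months that go unreported tend to be those where the aids are little used, the overall percentage describes the engaged part of the collaborative and not the collaborative. It could even rise as poorly engaged sites fall silent.

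The project's main question is scale-up. Phase 1 is five academic centers, four of which took part in the earlier randomized trial of the aids. They start first and have a mandatory initiation visit. Phase 2 is up to 32 more varied sites for which that visit is optional. An overall figure mixes the two, and the plan names no phase-specific figure.

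**Working it through.** The document gives no reach target, expected response rate or sample size, so there is no figure to reproduce. The check has two parts.

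**1. Does a silent site-month enter the overall figure?**

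- Numerator: site reports, plus site-specific online accesses.
- Denominator: eligible patients as judged by the site's surgeons. Website tracking counts downloads and clicks, not eligible patients. Staff have no access to site health records. No other source is named.
- The qualifier about sufficient data can be read in two ways. If it limits both the overall and the by-site figures, silent sites are excluded by rule. If it limits only the by-site figures, a silent site-month still supplies no eligible count and adds nothing to the overall percentage. The result is the same.
- Lack of responsiveness is one of two criteria for calling a site inactive. Replying with reach data is the example of communications engagement, which the plan itself lists as possibly associated with high reach. On the plan's own hypothesis, reporting and reach are related.

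**2. How large could the effect be?**

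Input from the document: at most 5 + 32 = 37 sites (N). Assumed: equal eligible volume per site, s silent sites, reporting-site reach R, silent-site reach Q.

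All-site reach = [(N − s) × R + s × Q] / N. Overstatement by the reporters-only figure = (s / N) × (R − Q). The bounds set Q = 0 and Q = 1.

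With R = 60%:

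| Silent sites | Q = 10% | Q = 30% | Lower bound | Upper bound |
|---|---|---|---|---|
| 12 of 37 | (15 + 1.2)/37 = 43.8% | (15 + 3.6)/37 = 50.3% | 15/37 = 40.5% | 27/37 = 73.0% |
| 7 of 37 | (18 + 0.7)/37 = 50.5% | (18 + 2.1)/37 = 54.3% | 18/37 = 48.6% | 25/37 = 67.6% |

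The overstatement is about 10 to 16 points with 12 silent sites, and about 6 to 9 points with 7.

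Over a wider grid (4 to 19 silent sites, R from 50% to 80%, Q at 0%, 20% or equal to R) it runs from 0, when silent sites have the same reach as reporting sites, to 41 points, with 19 of 37 silent at 0% and reporters at 80%: 19/37 × 0.80 = 0.411.

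**The case against.** The strongest reply has four parts.

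- **The qualifier may concern only small sites.** A by-site percentage from a handful of patients is unstable, and leaving it out is sensible. This is a fair reading, so the sentence should not be taken as a clear rule excluding sites from the overall figure. The point survives because the missing denominator has the same effect.
- **Missing-data rules belong in an analysis plan that is not shown.** This is right for the threshold of sufficient data, and its absence is no finding. But a later plan cannot readily recover eligible volume from sites that have stopped answering, so that item has to be collected prospectively.
- **Attrition is already disclosed under Adoption, and RE-AIM keeps adoption and reach apart.** Active and inactive counts will be reported, which helps the reader. They are not tied to the reach figure and do not correct it. The separation is, however, a good reason not to make a zero-filled figure the headline.
- **Silence is not failure.** A busy clinic may use the aids and not reply, and downloads may show that it does. This stands.

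A reader might infer more than the text supports:

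- That the result omits the sites where implementation failed. Sites that reply with low reach stay in, and a site that goes silent later may keep its earlier months.
- That the plan predicts missing reports. The Discussion says only "One practical limitation in this project is the challenge of engaging with busy clinicians" and speaks of tailoring communication.
- That four phase 1 sites had already used the aids. The text says only that they participated in the trial, which compared the aids with usual care.
- That phase 2 cannot be seen at all. By-site results allow it to be read for sites with enough data.

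**Conclusion.** The point holds in a limited form. As the plan stands, overall reach is a reporters-only percentage under either reading of the qualifier, and its missing data are plausibly informative. Upward bias is the likely direction, on the plan's own hypothesis that engagement goes with reach, but it is not certain. The size cannot be determined from the document. The contrast of 60% with 44-50%, and bounds of 41% and 73%, rests on assumed values for the number of silent sites, both reach levels and equal volumes. Bias is zero if silent sites match reporting sites.

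Nor do the documents support replacing the headline with a zero-filled figure. In the same illustration it gives 40.5% where the assumed truth is 43.8-50.3%, which is 3 to 10 points too low, and it mixes site attrition into patient reach.

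**What to change.** 1. Ask each site at joining, for example with the letter of support, for its usual monthly number of eligible patients, and record the date on which it begins implementation.
2. Keep the reporters-only percentage and label it as such.
3. Beside it, report lower and upper bounds for reach over all sites that joined and began implementation, including months after a site becomes inactive, up to the end of funding. Set unreported site-months to none reached and to all reached, using the site's own mean eligible volume or the volume stated at joining as denominator. Treat the zero-filled figure as a sensitivity bound.
4. Show recorded site-specific downloads for silent months as supporting evidence.
5. Give the number of sites and the share of site-months behind each figure, and say whether the sufficient-data condition applies to the overall figure or only to the by-site figures.
6. Report phase 1 and phase 2 separately as well as together.

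The cost is one extra question and a start date at joining, some analysis wording, and a wider and less favorable range in the report.

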#### Effectiveness

##### Data collection

Patient-level secondary outcomes include patient-reported shared decision making, assessed using the validated 3-item collaboRATE measure [32, 33], decisional conflict, assessed using the validated 4-item measure, SURE [34], integration of healthcare delivery, assessed using the validated 4-item measure, integRATE [35, 36], a self-developed question reporting the treatment chosen, and a one-item assessment of gist understanding from the validated Decision Quality Instrument for breast cancer [37].

We will utilize Qualtrics for patients to complete after their clinical encounter, if interested, at each site. This survey will be online, anonymous, and optional. The survey will include questions about the conversation aid, patient demographics, as well as the secondary outcomes listed above. The survey link and QR code will be available via postcards and/or clinic flyers given to patients or put in strategic locations in the clinic. We will offer a $20 USD gift card incentive to encourage the optional survey responses. Survey participants will be redirected to a separate survey to provide their email address and receive their gift card so that patient responses and email addresses remain separate.

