##### Evaluation

We will calculate descriptive statistics summarizing the NoMAD survey results for each phase 1 site at the conclusion of the implementation period.

Separately, we will use the factors shown from Table 1 as variables in a linear regression analysis to explore which factors might be associated with high levels of patient reach (clinical championship, team engagement, communications engagement etc.) and therefore might predict future patient reach. For these regressions, patient reach will be the dependent variable and each implementation factor will be an independent variable. We will assess each item at the site level so that “site” will be the unit of analysis. We will control for patient demographics and other potential sources of site heterogeneity, if possible.

Additionally, we will conduct mixed-effects linear or logistic regression analyses to examine the association between these implementation factors and our patient-reported outcomes. We will conduct an analysis for each outcome while controlling for patient demographics as fixed effects. For this analysis, “patient” will be the unit of analysis but we will account for clustering at the site level as a random effect.

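### A $20 anonymous survey whose link may be posted openly in the clinic, with payment details kept apart from answers, gives no described way to confirm eligibility or trace a repeat payee

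*Protocol article*

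**What the plan says.** The protocol article, Effectiveness – Data collection, sets out the collection method:

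- Mode: "This survey will be online, anonymous, and optional". Patients are to complete it after their clinical encounter.
- Access: the "survey link and QR code will be available via postcards and/or clinic flyers given to patients or put in strategic locations in the clinic".
- Payment: "We will offer a $20 USD gift card incentive to encourage the optional survey responses". A second survey takes the email address, "so that patient responses and email addresses remain separate".
- Content: "The survey will include questions about the conversation aid, patient demographics, as well as the secondary outcomes listed above". Those outcomes include shared decision making, decisional conflict, integration of care, one gist-understanding item and "a self-developed question reporting the treatment chosen".

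Effectiveness – Evaluation groups these data by site and shows them on the dashboard once a site has five responses. Implementation – Evaluation then fits mixed-effects linear or logistic models of the patient-reported outcomes on the Table 1 implementation factors, with site as a random effect: "We will conduct an analysis for each outcome while controlling for patient demographics as fixed effects". Receipt of a conversation aid is not named in these models.

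**The concern.** Each of the three stated features is reasonable alone: a link that may be posted in the clinic, a cash-equivalent incentive, and payment details kept apart from answers. Together they remove the usual safeguards on who is in the file. A posted QR code can be scanned by a companion, by a patient with no early-stage surgery decision, or by the same person again, and each completion leads to a gift-card form. If the payment list shows the same address twice, the separation means that the form cannot tell the team which answers to set aside.

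All patient-reported secondary outcomes, the dashboard and the patient-level models rest on this one file. The survey also asks about the conversation aid, but no described summary separates respondents who report receiving one from those who do not. A site's figure may therefore mix the two groups in unknown proportion.

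**Working it through.** The article states no survey sample size, response rate or invalid share, so there is no planned figure to reproduce. The first step compares the passages. The others are illustrations under assumed shares, not estimates for this project.

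**1. What the text allows**

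- *Eligibility.* Reach – Data collection has surgeons judge eligibility, but for the reach denominator. No link from that judgement to survey access is described, and a posted flyer bypasses it.
- *Repeat answers.* The email form is the only described place where a person is identifiable, and it is deliberately unlinked. It could limit repeat payments, but it cannot point to the repeated answers.
- *What could still be screened.* The items on the aid, demographics, treatment chosen and gist understanding could flag some implausible or unexposed respondents.
- *Receipt of an aid.* The Table 1 factors are rated per site and per month or quarter, so none records whether a given respondent received an aid.

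**2. Effect of invalid answers on a pooled proportion**

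Let p be the true top-score share, f the invalid fraction and q the top-score share among invalid answers. The observed share is (1 − f)p + fq. Assume p = 0.60, with q from 0.10 to 0.90:

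- f = 0.20: 0.80 × 0.60 + 0.20 × 0.10 = 0.50, and 0.48 + 0.20 × 0.90 = 0.66.
- f = 0.30: 0.70 × 0.60 + 0.30 × 0.10 = 0.45, and 0.42 + 0.30 × 0.90 = 0.69.

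**3. The dashboard threshold of five responses**

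One answer is 1/5 = 20% of a site's data at the threshold. The chance of at least one invalid answer among five is 1 − (1 − f)^5, if answers are independent:

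| Assumed invalid fraction f | Chance of at least one in five |
|---|---|
| 5% | 0.23 |
| 10% | 0.41 |
| 20% | 0.67 |
| 30% | 0.83 |

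**4. Repeat answers and precision**

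If a fraction d of people answer twice, identically, the Kish effective sample size divided by the number of responses is (1 + d)/(1 + 3d):

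- d = 5%: 1.05/1.15 = 0.91
- d = 10%: 1.10/1.30 = 0.85
- d = 20%: 1.20/1.60 = 0.75

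**5. Mixing respondents with and without an aid**

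If a fraction u received no aid, an effect that acts only through the aid keeps 1 − u of its size in the pooled group: 90%, 75% and 50% for u = 10%, 25% and 50%.

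**The case against.** The strongest reply is that a journal article condenses a fuller protocol. Screening items, duplicate checks and exclusion rules are the kind of detail left to that document, and the stated target is patients after their encounter. This stands in part: the article's silence does not show that such rules are absent. But open placement, payment and separation of emails are stated choices, and the point rests on those.

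Four stronger readings are tempting, and the documents do not support them.

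- *That invalid answers can never be removed.* The planned items could expose some of them, and the platform may have controls that the article does not mention.
- *That the patient-level models are wrong because they lack a term for receiving an aid.* They ask how site engagement relates to outcomes, which is an implementation question. The Background says that the aids were already tested in a randomised trial. Receipt may well lie on the path from engagement to outcome, so adjusting for it could block part of the association under study. A comparison by receipt would also be confounded by who is offered, or recalls, an aid.
- *That the evaluation needs a survey wave before the aids are introduced.* That would be a different design, and this weakness does not call for it.
- *That the primary outcome is compromised.* Reach is built from site reports and website access counts. Table 1 does score whether patient surveys were collected, and that score is one candidate predictor in the site-level reach regression, but it does not enter the measurement of reach.

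**Conclusion.** The point holds as a weakness in a stated collection method. As described, the survey offers no way to confirm that a respondent is an eligible patient, and none to connect a repeat payee to an answer. It affects the secondary patient-reported outcomes, the dashboard and the patient-level mixed models, and leaves patient reach alone.

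Its actual size is unknown. The range of 50% to 66% around a true 60% rests on an assumed 20% of invalid answers and an assumed 10% to 90% top-score share among them. The duplicate and dilution figures likewise use assumed shares. The only figure that follows from the plan itself is that one answer in five is 20% of a site's data at the dashboard threshold. That threshold governs display and is not an analysis sample size. This is an inexpensive improvement worth making, not a flaw that undermines the project.

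**What to change.** 1. Print a random single-use code with a site prefix on each postcard and hand the postcards out after the consultation. The code is not tied to a name, opens the survey once and releases one gift-card form. Answers and email addresses can stay separate as planned.
2. Give posted flyers their own tagged link. Leave those answers out of the main analysis and out of payment.
3. Using the questions on the conversation aid that are already planned, also report each patient-reported outcome by self-reported receipt of an aid. Do this as a descriptive stratification, or as a sensitivity restriction beside the mixed models in Implementation – Evaluation. It should not replace the implementation factors as the exposure.
4. If screening or duplicate rules already exist in a fuller document, state them or refer to them.

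The codes need to be in place before collection, because anonymous, unlinked answers cannot be matched afterwards. The cost is survey set-up and postcard printing, and probably somewhat fewer responses.
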